#### **11.1.1. Study Objectives and Variables of Interest**

The primary and secondary objectives of this clinical trial are to assess the impact on the vaginal microbiome of the use of a vaginal ring intermittently (3 weeks followed by 1 week off) or continuously (primary objective), to assess the general safety of the CVR (secondary objective 1), to assess vaginal biofilm formation and, to detect the presence or absence of a biofilm on the CVRs after intermittent or continuous use (secondary objective 2), and to determine the impact of intermittent or continuous use of the CVR on markers of inflammation and immune activation in the vagina (secondary objective 3).

The objectives will be reached by describing and comparing the variables of interest in women randomized to either intermittent vaginal ring use (group A) over a 12 week study period or continuous ring use (group B) over a 13 week study period.

The variables of interest are:

*Primary:* Changes from baseline (pre-ring use) in vaginal bacterial counts and in the absence/presence of BV-related bacteria as measured with quantitative real time PCR. Specifically, the flora species under study will include (but may not be limited to) the following species

- a. Total *Lactobacillus* count
- b. *Lactobacillus crispatus*
- c. *L. iners*
- d. *L. jensenii*
- e. *L. gasseri*
- f. *L. vaginalis*
- g. *Atopobium vaginae*
- h. *Gardnerella vaginalis*

*Secondary:*

1. Incidence of self-reported vaginal symptoms and clinician-observed signs  
Specifically:
  - a. Incidence of self-reported urogenital symptoms: any ring-use emergent cases of irritation, burning, itching, discharge, bleeding, pain
  - b. Incidence of genital signs on examination: any ring-use emergent cases of vaginal discharge, erythema, edema, ulcer, condyloma, petechia, ecchymosis, peeling
2. Incidence of BV as defined as a Nugent score >6
3. The numbers of women prematurely withdrawing from the study or discontinuing ring use
4. Incidence of adverse experiences during ring use and serious adverse experiences during or within 7 days after ring use
5. The numbers of incident STIs (HIV, HSV-2, Syphilis, Trichomoniasis, Chlamydia, Gonorrhea) and candidiasis
6. Nugent scores and Ison & Hay grading of the vaginal flora
7. Changes in phenotype of BV-related bacteria: specifically
  - i. Presence of dispersed forms of bacteria
  - ii. Presence of adhesive forms of bacteria on epithelial cells
8. Presence or absence of a biofilm on the CVRs after intermittent or continuous use
  - b. Presence of biofilm visualized by crystal violet
  - c. Visualization of adherent bacteria using FISH
  - d. Identification of adherent bacteria (including but not limited to *Lactobacilli* sp., *G. vaginalis*, *A. vaginae*)
9. Changes in inflammatory cytokines concentrations in CVLs as measured by Luminex technology. The cytokines analyzed include, but are not limited to IL-1, IL-6, IL-8, IL-10.

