#### 8.1.1.2. Baseline visit (week 0)

First, women will be interviewed face-to-face using an IAQ. The IAQ will include questions about demographic characteristics, sexual behaviour, medical history and reproductive history, current medication, menses information and acceptability of the CVR.

The following procedures will also be carried out:

- A pelvic examination:
  - A total of 3 vaginal swabs will be collected:
    - One cotton swab for Wet Mount [*Trichomonas vaginalis* (TV); *Candida albicans*] and smears for BV diagnosis;
    - Two regular flocked swabs (Copan, Italy) for the characterisation of the vaginal microbiome.
  - A total of 2 cervical swabs will be collected for *Neisseria gonorrhoeae* (NG) and *Chlamydia trachomatis* (CT) testing. One swab will be processed immediately for the rapid detection of CT. The other regular flocked swab will be used for molecular testing of CT/NG.
  - A CVL for the detection of inflammatory processes.
- A physical examination of other body systems will be performed with special attention to the cardiovascular system.
- Collect blood by venepuncture (5 ml) in a serum tube and test for HIV according to the national HIV algorithm, and for syphilis and herpes simplex type 2 (HSV-2).
- A urine sample will be obtained for testing for pregnancy and an aliquot of fixated urine for FISH analysis will be stored at 2-8°C until shipment to ITM.
- All women will be offered risk reduction counselling, including pre- and post-test HIV counselling and condoms free of charge.
- Curable genital infections will be treated at the study site free of charge.
- Any other medical conditions – including newly diagnosed HIV – will be referred to local referral hospitals or clinics.

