- The pelvic and general physical examinations will be performed as at baseline. A total of 3 vaginal swabs are collected for:
  - One cotton swab for Wet Mount [*Trichomonas vaginalis* (TV); *Candida albicans*] and smears for BV diagnosis;
  - Two regular flocked swabs (Copan, Italy) for the characterisation of the vaginal microbiome.
- At visit 6 for Group A and visit 5 for Group B, after the final ring has been removed and all other vaginal specimens have been collected, a CVL sample will be collected.
- A urine sample is obtained, tested for pregnancy and an aliquot of fixated urine will be stored for FISH analysis.
- A completed diary card will be collected at each visit and a new diary card will be provided. Any problems with ring use will be addressed.
- The removed ring will be processed according to the instructions provided by the ITM and stored for biofilm analysis.
- Risk reduction counselling will be provided as well as condoms (free of charge).
- During the last ring removal visit (V6 for group A and V5 for group B) the following additional procedures will be offered:
  - a Visual Inspection with Acetic acid (VIA) to identify women at risk for cervical cancer;
  - An HIV test according to the national HIV algorithm. A maximum of 5 ml of blood will be collected by venepuncture in a serum tube. Pre- and post-test HIV counselling will be provided.

Additional questionnaires during ring removal visits:

1. The IAQ will be performed at every visit and will assess adherence and acceptability of the ring use but will be more comprehensive at visits 4 and 6 for group A and at visits 3 and 5 for group B. It will also assess factors that might influence the vaginal microbiome and vaginal inflammation.
2. Between weeks 7 and 9, 16-24 women will be enrolled in one of two FGD in each randomization group, for a total of four FGD.

3. At the last ring removal visit, and if funding permits, all study participants will be invited to provide their feedback on experiences with the new contraceptive method, on acceptability and adherence using ACASI.

The following procedures are performed at the ring insertion visits for group A:

- Information on adverse events, social harms and concomitant medication will be collected.
- Risk reduction counselling will be provided as well as condoms (free of charge).

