#### **8.4.3. Stored specimens**

The left-overs of the urine, blood and vaginal/cervical specimens, collected during the clinical study will be stored at RU or at ITM as defined in the analytical plan. Aliquots of vaginal swabs, blood, and urine will remain at RU as back-ups. These specimens may be used for repeat and confirmatory analyses to arrive at a proper diagnosis and/or for future research testing (see above). These study samples will be destroyed after the final study report has been issued, except as indicated in “8.2 Obtaining Informed Consent”.

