#### 11.1.2.4. Secondary analyses

The incidence of signs and symptoms, study/ring use withdrawals, adverse experiences, and STIs will be compared among randomization groups over the full study period using Fisher's exact test. Changes in Nugent scores and Ison & Hay grading of the vaginal flora will be graphically depicted and analyzed using repeated measures (logistic) regression models.

Analyses of endpoints related to secondary objectives 2 and 3 will be research and data driven. Presence/absence of dispersed/adherent form of BV-related bacteria and of biofilms will be analyzed using repeated measures logistic regression models.

Analyses of CVLs will focus on changes from baseline in cytokine concentrations. Care will be taken to mitigate the influence of truncation of the concentration data due to samples below or above the quantification limit of the assays used. Data reduction techniques as PCA may be used to summarize the multidimensional data in a limited number of variables. All samples that are showing elevated cytokine levels, as well as an equal number of controls not showing elevated cytokine levels, will be tested further for the presence of other proteins involved in inflammatory pathways. Control samples will be selected matched on major prognostic factors.

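### Incident chlamydia, gonorrhea, syphilis and HSV-2 are part of a secondary safety endpoint, but the visit procedures name tests for them only at baseline

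*Protocol*

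**What the plan says.** **Endpoint and analysis.** Section 11.1.1 defines secondary endpoint 5 as "The numbers of incident STIs (HIV, HSV-2, Syphilis, Trichomoniasis, Chlamydia, Gonorrhea) and candidiasis". The synopsis and section 6 place incident STIs under general safety. Section 11.1.2.4 states that "adverse experiences, and STIs will be compared among randomization groups over the full study period using Fisher's exact test".

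**Baseline.** In section 8.1.1.2, "A total of 2 cervical swabs will be collected" for gonorrhea and chlamydia: one for the rapid chlamydia test and one for molecular testing of both. A 5 ml serum tube is tested for HIV, syphilis and HSV-2. A vaginal swab gives the wet mount for trichomonas and candida.

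**Follow-up.** Section 8.1.3 says of each ring removal visit that "A total of 3 vaginal swabs are collected for" the wet mount, the BV smears and the microbiome. At the last removal (V6 in group A, V5 in group B) it adds a CVL and an offered HIV test, for which "A maximum of 5 ml of blood will be collected by venepuncture in a serum tube". It names no cervical swab, no CT/NG assay and no syphilis or HSV-2 test.

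**Elsewhere.** Section 8.4 lists CT/NG, HSV-2 and syphilis testing among the diagnostic tests without naming a visit. Section 8.4.1 places the rapid chlamydia swab at baseline. Section 8.4.3 says that "Aliquots of vaginal swabs, blood, and urine will remain at RU as back-ups".

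**The concern.** A count of incident infections needs a result after baseline in women who were free of the infection or treated at baseline. For four of the six named STIs, the procedures as listed do not produce that result in a systematic way.

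The report would then show few or no incident chlamydia, gonorrhea, syphilis or HSV-2 infections in either arm, beside a non-significant Fisher test, under the heading of general safety. The rationale in sections 4.1 and 4.2 concerns vaginal safety where HIV and STI risk matter, so readers would be inclined to take that as reassurance. Any cases that did appear would come from symptoms, syndromic diagnosis or unscheduled attendance. In an open-label trial with three pelvic examinations during ring use in one arm and four in the other, that kind of detection may differ between arms.

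A statistical analysis plan cannot repair this, because it cannot create specimens or assays.

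**Working it through.** **1. The plan's own figure.** The plan gives no STI incidence and claims no power for this endpoint. Its only sample size figure is 52 evaluable women per group for the primary pre-post change (11.1.3). With 95% power, two-sided 5% and change/SD = 0.5/1 (or 1.5/3), the paired formula gives n = ((1.960 + 1.645) / 0.5)² ≈ 52. The figure reproduces, and the present point does not touch it.

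**2. Tests named per infection.** Ring removal visits are V2, V4 and V6 in group A, and V2 to V5 in group B (8.1.8).

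| Infection | Baseline (8.1.1.2) | Named in follow-up (8.1.3), per woman |
|---|---|---|
| Chlamydia | cervical swabs: rapid and molecular | 0 |
| Gonorrhea | cervical swab: molecular | 0 |
| Syphilis | serum | 0 |
| HSV-2 | serum | 0 |
| HIV | serum | 1, offered at the last removal |
| Trichomonas, candida | wet mount | 3 (group A) or 4 (group B) |

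Four of the six STIs have no named follow-up test.

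**3. Does other wording supply the tests?**

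- *Examination repeated from baseline.* Section 8.1.3 says that the pelvic and general examinations follow the baseline ones, and at baseline the cervical swabs sit under the pelvic examination. But so does the CVL. Section 8.1.3 then restates the three vaginal swabs and adds a CVL at the last removal only. If the phrase carried all specimens forward, a CVL would be due at every removal and neither statement would be needed.
- *Schedule of assessments.* The rows for week 12 (group A) and week 13 (group B) use the same sample wording as baseline: blood, vaginal swabs with CVL, and urine. The baseline row itself names no cervical swab or serology. The table therefore shows neither that the tests are repeated nor that they are dropped.
- *Stored and batched specimens.* Section 8.2 allows stored samples to be used for tests already specified in the protocol and run in batches. Section 8.4.3 keeps back-up aliquots. This permits testing but does not schedule it.

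**4. Size, under stated assumptions.** The documents give no incidence, so a range is assumed. Expected true cases per infection = 104 × p. Expected counted cases = 104 × p × s, where s is the assumed share found syndromically or at unscheduled visits.

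| True cumulative incidence p | True cases | Counted, s = 0 | s = 10% | s = 30% |
|---|---|---|---|---|
| 1% | 1.0 | 0 | 0.1 | 0.3 |
| 2% | 2.1 | 0 | 0.2 | 0.6 |
| 5% | 5.2 | 0 | 0.5 | 1.6 |
| 10% | 10.4 | 0 | 1.0 | 3.1 |

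At p = 5% and s = 30%, the chance of counting no case at all is (1 − 0.05 × 0.3)^104 = 21%. With a fully sensitive test in every woman it is (1 − 0.05)^104 = 0.5%.

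For an assumed 5% against 15% with 52 women per arm, the power of Fisher's exact test is 26% with full ascertainment and 1.4% with s = 30%. It rounds to zero with s = 10%.

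**The case against.** The strongest case on the other side is that the text is under-specified and does not exclude repeat testing. The examination is said to repeat baseline, and the last-visit row of 8.1.8 matches the baseline row. The last serum tube may hold as much as the baseline tube that served HIV, syphilis and HSV-2. Section 8.4 does not limit the assays to baseline. Sections 8.2 and 8.4.3 leave room for batched testing, and specimen handling is deferred to an analytical plan that is not at hand. Much of this stands: repeat testing may well have been intended. None of it assigns a test to a visit, and the explicit list in 8.1.3 points the other way.

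A reader might go further and infer that the four counts are zero by construction, or that these infections cannot be ascertained at all. The documents do not support that. Section 8.4 provides for syndromic diagnosis, 8.1.3 for a pelvic examination at every ring removal, and 8.1.5 for unscheduled visits, so some cases could be found. Stored specimens could also be tested. For the same reason it would be too strong to say that the Fisher comparison rests on trichomoniasis and HIV alone. Nor can 8.1.8 be used to show that the tests are dropped.

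It is also fair that this affects part of one of nine secondary variables, and that power for STIs would be low even with complete testing.

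**Conclusion.** The point holds as an inconsistency between secondary endpoint 5, with its Fisher comparison, and the follow-up procedures in 8.1.3. Chlamydia, gonorrhea, syphilis and HSV-2 are not systematically ascertained after baseline.

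If 0 to 30% of cases are found syndromically and true incidence is 1 to 10%, the expected count per infection is 0 to about 3, against about 1 to 10 true cases. Incidence, detection share and a fully sensitive comparator test are assumptions; the count of named follow-up tests is not. The loss of power matters less than the meaning of the result: a low count would show that few women were tested, and would say little about ring safety.

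The primary endpoint and its sample size are unaffected. This should be fixed, but it does not undermine the trial.

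**What to change.** Reconcile 8.1.3, 8.1.8, 8.4 and 11.1.1 together, in one of two ways.

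**(a) Name the tests.** At the last ring removal visit (V6 in group A, V5 in group B), specify syphilis and HSV-2 serology on the serum already drawn. Specify CT/NG molecular testing on a stored follow-up vaginal swab, if the laboratory confirms that this specimen suits its method. The urine aliquot described in 8.1.3 is fixated for FISH, and nothing in the protocol shows that it is suitable. State that the specimen changes from the baseline cervical swab. Count as incident only women who were negative or treated at baseline. *Cost:* assays on existing specimens for about 104 to 120 women, with serology missing for those who decline the offered blood draw.

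**(b) Narrow the endpoint.** Restrict endpoint 5 and its Fisher test to trichomoniasis, candidiasis and HIV. Report the other four infections as baseline prevalence, and list any symptomatic follow-up cases descriptively. *Cost:* wording only, with a narrower safety endpoint. The report should still state that wet mounts number three in group A and four in group B.

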## **11.1.2. Statistical methods**

### 11.1.2.1. Analysis populations

In general, analyses will be performed using an "as-randomized" all-patients-treated approach. All women randomized to either group and who insert the CVR at the enrollment visit will be included in the analysis under the group they are randomized to, even if they discontinue before visit 2 (week 4). For the analyses requiring vaginal or urine samples, all women with available data will be used, i.e. women without a sample prior to or during CVR use will be excluded.

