| Social Science Component | To assess the level of acceptability and reported adherence to intermittent and continuous CVR use in women in Rwanda.              | Lost to follow up rate; rate of discontinuation (base on clinical trial data).
Level of adherence based on self-reported adherence scale and diary cards.
Qualitative description of user experiences, relationship attributes, and sexual encounter attributes.
Reported vaginal practices and beliefs regarding menstruation and impact on ring adherence.
Reported reproductive health symptoms and impact on adherence.
Number of women envisaging future use of contraceptive ring. |
| Study Method             | Secondary objectives                                                                                                                | Secondary endpoints                                                                                                                                                                                                                                                                                                                                                                                                                                                                                     |
| Clinical Trial           | To assess the general safety of the CVR.                                                                                            | Incidence of self-reported vaginal symptoms and clinician-observed signs
Incidence of BV.
The numbers of women prematurely withdrawing from the study or discontinuing ring use.
Incidence of adverse and serious adverse experiences .
The numbers of incident STIs and candidiasis.
Nugent scores and Ison & Hay grading of the vaginal flora.                                                                                                                                         |

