## **7.4. Randomization and blinding**

This is an open-label study because the differences in ring use (intermittent or continuous use) cannot be blinded. Individual participants will be randomized and treatment allocation will be concealed until a participant has provided informed consent, confirmed eligible, and is included in the study. Randomization will be done at enrolment using randomization envelopes, specifying the treatment group.

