#### **8.1.2. Enrolment visit (at the start of week 1)**

Women will be invited for the enrolment visit which will take place on the first day of their menstrual cycle. (ie. the first day of menstrual bleeding). A visit window of + 1 day will be allowed when the menstrual cycle starts on a Sunday or bank holiday. The visit can be rescheduled maximum once if the participant is not on her first day of menstrual bleeding (+ 1 day).

All test results from the baseline visit will be reviewed, and eligibility will be confirmed. Eligible women will be randomized either to an intermittent regimen (group A) or an extended (continuous) regimen (group B) of ring use.

There will be no re-screenings.

The following procedures will also be carried out:

- The general physical examination will be performed as at baseline.
- All women will be offered risk reduction counselling and condoms free of charge.
- A urine sample will be obtained for pregnancy testing.
- Study staff will teach women how to use the ring and study participants will be asked to insert the ring while still at the study clinic.

- A questionnaire on acceptability of the ring after the ring has been inserted.
- Participants will receive a diary card and will be explained how to complete a diary card regarding ring use and sexual behaviour as well as how to complete a self-rating adherence scale.
- Provide a follow-up visit date: 3 weeks after the enrolment date.

### 8.1.3. Follow up visits: Visits 2 to Visits 6

The follow up visits are planned to coincide with times of removal and insertion of the ring. Women in group A will visit the clinic at days of removal and insertion. These visits will coincide in group B as the old ring will be replaced by a new one at the same visit.

Participants in group B will be allowed to complete each follow-up visit up to three days prior/after their scheduled visit. The visit window for participants in group A (intermittent use) will depend of the kind of visit. Ring removal visits can be delayed for a maximum of 2 days, ring insertion visits can be performed a maximum of 2 days in advance. Every effort should be made to ensure participants adhere to this visit schedule.

The following procedures are performed at each ring removal visit (both study arms):

- Information on adverse events, social harms and concomitant medication will be collected.

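### Randomised women who do not insert the ring are left out of the withdrawal and discontinuation comparison

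*Protocol*

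**What the plan says.** Section 11.1.2.1 of the protocol opens its rule with "In general, analyses will be performed using an 'as-randomized' all-patients-treated approach" and then defines the set: "All women randomized to either group and who insert the CVR at the enrollment visit will be included in the analysis". Women are kept in their allocated group even if they stop before visit 2. One further rule narrows the set for sample-based analyses: "women without a sample prior to or during CVR use will be excluded". No wider set is named for endpoints that need no sample.

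Allocation is open. Section 7.4 says "This is an open-label study because the differences in ring use (intermittent or continuous use) cannot be blinded". Section 8.1.2 places randomisation and first insertion at the enrolment visit: "Eligible women will be randomized either to an intermittent regimen (group A) or an extended (continuous) regimen (group B) of ring use", and later in the same section "study participants will be asked to insert the ring while still at the study clinic".

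The endpoints affected are secondary endpoint 3 in section 11.1.1, "The numbers of women prematurely withdrawing from the study or discontinuing ring use", which section 11.1.2.4 compares between the groups with Fisher's exact test, and a primary endpoint of the social science component in section 6, "Lost to follow up rate; rate of discontinuation (base on clinical trial data").

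Section 7.5 classes a woman who tells staff that she is ending her participation as an early withdrawal. It sets no condition that she must have used a ring.

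**The concern.** The analysis set is conditioned on something that happens after an open allocation. For most clinical endpoints this does little harm. For withdrawal and discontinuation it removes possible cases of the outcome itself. A woman who learns her regimen and leaves before inserting the ring is a withdrawal under section 7.5, but section 11.1.2.1 takes her out of the population in which withdrawals are compared.

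Two things are at stake. The withdrawal and discontinuation rate is understated in any group with non-inserters. If non-insertion differs between regimens, the comparison loses part of the difference it is meant to show. The protocol's own rationale (section 4.2) asks whether continuous use is acceptable to women who will no longer have a regular cycle, so refusal of a regimen bears on the trial's question.

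**Working it through.** **Step 1. Follow one woman through the text.** She is randomised at the enrolment visit, does not insert the ring, and tells staff she is leaving.

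| Protocol section | How she is treated |
|---|---|
| 7.5 Handling of withdrawals | Early withdrawal; reason and date recorded on the CRF |
| 11.1.2.1 Analysis populations | Not in the general analysis set |
| 11.1.2.2 Baseline characteristics | Can appear in the tabulation of discontinuations by reason and visit, and in the CONSORT diagram |
| 11.1.2.4 Secondary analyses | Absent from the Fisher comparison, since no other set is named |
| 6, social science primary endpoints | Absent from the discontinuation rate if it is computed in the clinical analysis set |

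Sections 7.5 and 11.1.2.1 therefore disagree about her for the withdrawal endpoint.

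**Step 2. The plan's own figures.** Section 11.1.3 gives 52 evaluable and 60 randomised women per group. With 95% power, two-sided 5%, a change of 0.5 log and an SD of 1, the within-group formula is n = ((1.960 + 1.645) × 1 / 0.5)² = 51.98, so 52. The allowance for loss is (60 − 52)/60 = 13.3%. Neither figure depends on this point. A non-inserter has no sample during ring use and is out of the microbiome analysis anyway.

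**Step 3. Effect on a single rate.** Let k be the women in a group of 60 who do not insert, and d those who discontinue later.

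- Ring-inserted set: d / (60 − k)
- All randomised: (d + k) / 60

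Each non-inserter is 1/60 = 1.7 percentage points of the group; k = 1 to 5 omits 1.7% to 8.3% (5/60). With the assumed k = 3 and d = 6, the two rates are 6/57 = 10.5% and 9/60 = 15.0%. With k = 0 they are equal.

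**Step 4. Effect on the between-group test.** The protocol gives no non-insertion rate, so every count below is an assumption. All non-insertion is placed in group B, the arrangement that affects the comparison most. The top of the range, k = 8, equals the whole loss allowance per group (60 − 52). Percentages are for group B; p is Fisher's exact, two-sided.

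| Later discontinuations A, B | k in B | Ring-inserted set | p | All randomised | p |
|---|---|---|---|---|---|
| 5, 5 | 0 | 5/60 v 5/60 (8.3%) | 1.00 | 5/60 v 5/60 (8.3%) | 1.00 |
| 5, 5 | 1 | 5/60 v 5/59 (8.5%) | 1.00 | 5/60 v 6/60 (10.0%) | 1.00 |
| 5, 5 | 4 | 5/60 v 5/56 (8.9%) | 1.00 | 5/60 v 9/60 (15.0%) | 0.39 |
| 5, 5 | 8 | 5/60 v 5/52 (9.6%) | 1.00 | 5/60 v 13/60 (21.7%) | 0.071 |
| 5, 8 | 6 | 5/60 v 8/54 (14.8%) | 0.38 | 5/60 v 14/60 (23.3%) | 0.043 |

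The conclusion of the test moves only when non-insertion is both frequent and unequal. Equal non-insertion lowers both reported rates but introduces no difference between the groups.

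**The case against.** The case for leaving the rule alone has weight, and most of it narrows the point.

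- **The rule is stated for the general case**, and section 11.1.2.2 tabulates discontinuations among enrolled women by reason and visit. A reader might infer that non-inserters vanish from every analysis. The text does not support that; what they are missing from is the formal comparison.
- **Acceptability.** A reader might also infer that acceptability is measured only in women who accepted the ring. It is analysed under section 11.2, which states no such restriction, and section 8.1.1.2 asks about it at baseline, before randomisation. Only the enrolment questionnaire follows insertion.
- **Order of events.** It is tempting to say that counselling, examination and pregnancy testing all fall between the envelope and insertion. Section 8.1.2 gives an unordered list, section 8.1.8 lists counselling before randomisation, and section 7.4 conceals allocation until eligibility is confirmed. How much time a woman has to reconsider is not fixed.
- **Non-insertion is probably rare.** Willingness to use the ring is an inclusion criterion, and section 4.1 cites a placebo-ring study in which most women were comfortable with insertion. Both groups wear the same ring for the same first three weeks, so a woman who dislikes her regimen may well stop later, when she is counted.
- **A treated set is conventional for safety**, and discontinuing presupposes starting. That is fair for adverse events during ring use. It does not cover study withdrawal, which is part of the same endpoint.
- **The SAP may define another denominator.** It is not at hand. But the protocol does not leave this open: it states a rule, and the withdrawal endpoint has no exception to it.

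**Conclusion.** The point holds in a limited form. Under section 11.1.2.1 a woman who leaves between allocation and insertion is excluded from the withdrawal and discontinuation endpoints, although section 7.5 counts her as a withdrawal. The restriction reaches the Fisher comparison in section 11.1.2.4 and, if computed in the same set, the discontinuation and loss-to-follow-up rates used by the social science component. It does not touch the primary microbiome result, and the documents do not support extending it to acceptability in general.

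Its size cannot be stated from the protocol. The bias is zero if every randomised woman inserts the ring and 1.7 percentage points of a group for each who does not. A changed test result needs several non-inserters concentrated in one group, which the shared first three weeks make unlikely. This is a minor point, worth correcting because the correction is nearly free.

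**What to change.** Add one sentence to section 11.1.2.1: for study withdrawal, ring discontinuation and loss to follow-up, all randomised women are analysed in their allocated group, with non-insertion at enrolment counted as an event at day 0. State that the social science discontinuation rate uses the same denominator. Keep the ring-inserted set for the microbiome and adverse-event analyses.

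Report non-insertion by group, with reasons, on its own line. Discontinuation would otherwise mix women who never started with women who stopped, which is the one drawback of the change. With a separate line, a reader can recover either definition.

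The cost is wording only. Section 7.5 already requires the reason and date of discontinuation on the CRF, so no new data are needed, and the sample size is unaffected.
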